### Statistical analysis

2.6

Analysis accounts for the cluster-randomization design, with schools as clusters and students nested within schools. Intention-to-treat (ITT) principles are applied, using SAS 9.4.

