#### Outcome analysis

2.6.2

Analysis will be performed following the intention-to-treat principle. Mixed-effects linear models (MLMs) will be used to evaluate changes in outcomes from baseline (T0) to post-intervention (T1) and follow-up (T2). The models will include group (intervention/control), time (T1, T2), and the group-by-time interaction as fixed effects, with the baseline value (T0) of the respective outcome included as a covariate. Individual-level intercepts will be fitted as random effects to account for repeated measurements, and school will be included as a random effect to adjust for the cluster-randomized design. The models will be further adjusted for prespecified covariates, including age, sex, and baseline physical activity level. The primary test for intervention effect will be the significance of the group-by-time interaction term.

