### Implementation evaluation

2.7

Implementation of fidelity and exposure will be assessed to validate intervention effects. Metrics will include:

(1) School-level compliance with the meal plan (e.g., provision of ≥50 g of coarse cereals per student per day).(2) Participant attrition rates at T1 and T2.(3) Comparison of overweight/obesity outcomes between compliant and non-compliant schools.(4) Individual-level adherence, which will be assessed based on the 3-day 24-h dietary recall data collected at T1. High adherence is defined as an estimated average daily coarse-cereal intake of ≥40 g, while low adherence is defined as an intake of <25 g.(5) A prespecified subgroup analysis comparing outcomes between participants with high adherence and those with low adherence.

Paired *t*-tests and standardized regression coefficients will be used to evaluate outcome changes and the impact of confounding factors. Analyses will adjust for confounding factors (e.g., age, sex, baseline BMI). The impact intensity of each variable will be determined using standardized regression coefficients.

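### Section 2.7 uses paired t-tests, which have no control arm, as a supporting evaluation of outcome changes; they cannot validate an intervention effect in growing children

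*Protocol article*

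**What the plan says.** Two sections give a method for changes in outcome.

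- **Section 2.6.2 (Outcome analysis)** uses mixed-effects linear models for change from baseline to T1 and T2. The fixed effects are group, time and their interaction, with the baseline value as a covariate. It then says: "The primary test for intervention effect will be the significance of the group-by-time interaction term".
- **Section 2.7 (Implementation evaluation)** opens with "Implementation of fidelity and exposure will be assessed to validate intervention effects". It lists five metrics, among them overweight and obesity outcomes in compliant versus non-compliant schools, and outcomes in high versus low adherers. It then says: "Paired *t*-tests and standardized regression coefficients will be used to evaluate outcome changes", and extends this to the influence of confounders. The next sentence promises adjustment for factors such as age, sex and baseline BMI.

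Section 2.7 does not say which outcomes, which arm or which time points the paired tests cover, nor how their results stand to those of section 2.6.2. It does not call them descriptive.

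**The concern.** A paired t-test asks whether the mean change in one set of children differs from zero. Participants are 8 to 12 years old, and section 2.5 places T1 at 3 months and T2 at 9 months. Over that time waist circumference, fat and lean mass, raw BMI and blood pressure can move through growth alone. A significant paired test then says nothing about the intervention.

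Upward drift can mislead in three ways:

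- The intervention arm appears to worsen.
- A true benefit is hidden, because growth offsets it.
- If the test is run in each arm, the control arm shows a significant rise and the intervention arm does not, and this is read as a benefit.

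The article intends its findings to inform national school-meal policy, so a p-value of this kind in a section meant to validate effects is an avoidable hazard.

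**Working it through.** **1. Does the test suit the section's own tasks?**

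- *Validating an intervention effect:* this needs a comparison with the control arm; a paired test has none.
- *Adjusting for age, sex and baseline BMI:* a paired t-test has no covariate terms.
- *Compliant versus non-compliant schools, high versus low adherers:* these compare different children; a paired test compares each child with itself.

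**2. How often would drift alone be significant?**

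The plan gives no figure for the paired tests, so there is none to reproduce. Inputs:

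- n = 180 children, the figure per school in section 2.3.1, used here only as a number of children analysed. Enrolment is 200 per group (section 2.3).
- Two-sided α = 0.05 (section 2.3.1).
- Intervention effect = 0 (the scenario under test).
- g = mean drift divided by the SD of the change score. This is an assumption, with range 0.10 to 0.30; the documents give neither a growth rate nor an SD of change.

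The rejection probability is P(|T| > t), where T is noncentral t with n − 1 degrees of freedom and noncentrality g√n. For n = 180, √n = 13.42 and t = 1.973.

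| g | g√n | paired test significant, n = 180 | n = 200 |
|---|---|---|---|
| 0.10 | 1.34 | 26.6% | 29.1% |
| 0.15 | 2.01 | 51.7% | 56.0% |
| 0.20 | 2.68 | 76.1% | 80.4% |
| 0.25 | 3.35 | 91.6% | 94.0% |
| 0.30 | 4.02 | 97.9% | 98.8% |

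An observed mean change of 1.973/13.42 = 0.147 SD is already significant at n = 180.

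As an illustration in centimetres, assume a waist drift of 0.5 cm with an SD of change of 4 or 3 cm (g = 0.125 or 0.167). The test is significant in 39% or 60% of cases. With 1.0 cm (g = 0.25 or 0.333) the figures are 92% and 99%.

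**3. The same drift in a between-arm contrast**

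Equal drift cancels. Simulated two-sample t-tests on change scores, 180 per arm and 4,000 trials per setting, rejected in 5.4%, 5.0% and 5.3% of trials for g = 0.10, 0.20 and 0.30. This assumes no school-level variation. It is a simple stand-in for the section 2.6.2 model, not that model itself.

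**4. If the paired test is run in each arm**

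Let p be the rejection probability from step 2. With equal drift, independent arms and no effect, the chance that the control arm is significant and the intervention arm is not is p(1 − p):

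- g = 0.10: 0.266 × 0.734 = 0.20
- g = 0.15: 0.517 × 0.483 = 0.25
- g = 0.20: 0.761 × 0.239 = 0.18
- g = 0.30: 0.979 × 0.021 = 0.02

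**The case against.** The strongest reply is that nothing in the article rests the effectiveness conclusion on a paired t-test. That is correct. A reader who sees only section 2.7 might infer that the trial judges its outcomes by before-after tests; section 2.6.2 rules this out by naming a primary test that uses both arms. The harm depends on how a supporting p-value is read.

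A second reply is that the purpose statement opens section 2.7, while the t-test sentence follows the list of metrics and names no outcome or arm. Adjustment may also be meant only for the regression part. Both readings are possible. But the t-test sentence stands in the same section with no limit on interpretation, and if the adjustment belongs to the regression, the paired tests are simply unadjusted.

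A third reply is that growth should not move BMI-SDS, the sample-size outcome, because it is age-standardised. This stands, and it confines the point to the other measures. The size also rests on assumed drift: step 2 shows that a one-sample test detects a non-zero mean, and it is not an error rate of the primary test.

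A reader might also object that paired tests ignore schools, although section 2.6 says that "Analysis accounts for the cluster-randomization design, with schools as clusters and students nested within schools", and might expect section 2.6.2 to repair this because "school will be included as a random effect to adjust for the cluster-randomized design". That argument does not favour one method over the other. Section 2.2 randomises two schools, one to each arm, so school and intervention coincide and the section 2.6.2 model cannot separate them either. The case here rests on the missing control comparison alone.

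**Conclusion.** The point holds as a defect in a supporting analysis. Section 2.7 fixes an uncontrolled before-after test for outcome changes, in a section whose stated purpose is to validate intervention effects, and that test cannot do this or the section's other tasks. These conclusions follow from the text and need no assumed number.

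The size does need one. With 180 children and drift of 0.10 to 0.30 SD of change, the paired test is significant in about 27% to 98% of cases without any intervention effect, against about 5% for a between-arm contrast under equal drift and no school-level variation. It applies to waist circumference, body composition, raw BMI and blood pressure, and only weakly to BMI-SDS. The primary test is not affected. The change should be made, because it removes a misleading result at almost no cost.

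**What to change.** - Remove the paired t-tests from section 2.7.
- Base every statement on intervention effect on the between-arm contrasts at T1 and T2 from the section 2.6.2 model, and say so in section 2.7. This removes the growth problem; it does not remove the limit set by one school per arm.
- Show within-arm change as mean and SD, or with a confidence interval, without p-values.
- Use covariate-adjusted regression for the adherence comparisons and label them exploratory, since adherence is not randomised.

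The cost is a few sentences in the protocol or analysis plan. No data collection changes, and the analysis becomes shorter.

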## Discussion

3

### Rationale and significance

3.1

Coarse cereals, including millet, naked oats, and buckwheat, have a long history in the Chinese diet (6). Despite dietary guidelines recommending 30–70 g of coarse cereals per day for children aged 7–13 years (22), average intake among Chinese children was 8 g/day in 2020. Concurrently, school meal programs in China are being standardized and widely implemented, providing a feasible platform to improve dietary quality and reach a large proportion of school-aged children (24, 25). By integrating coarse-cereal provision into daily meals, this intervention is culturally acceptable and likely to be supported by parents and schools.

This study protocol outlines a school-based pragmatic randomized controlled trial (pRCT) designed to evaluate the real-world effectiveness of a daily 50 g coarse-cereal substitution in preventing obesity among primary school students (grades 3–4, aged 8–12 years) (19). Unlike explanatory trials conducted under highly controlled conditions, this pRCT leverages existing school infrastructure and routine operational workflows to assess the intervention’s impact within the complex reality of the Chinese educational setting. The intervention combines dietary modification, multi-level nutrition education, and digital monitoring tools, addressing critical gaps in childhood obesity prevention research in China. By adopting a pragmatic design, this study aims to generate robust evidence on the feasibility, scalability, and practical effectiveness of coarse-cereal interventions, thereby directly aligning with national public health priorities and informing future policy implementation.

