#### Intervention group

2.4.1

Eligible students aged 8–12 years (grades 3–4) in the intervention school received daily coarse-cereal intervention incorporated into school meals, combined with structured nutrition education for students and parents.

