##### Student education

2.4.3.1

Students will attend 7 structured, interactive nutrition education sessions (approximately 45 min each, conducted twice per month). These sessions will be delivered by trained school health teachers or homeroom teachers using a standardized curriculum developed by the research team. The curriculum covers sequential topics including: (i) Introduction to Coarse Cereals and Their Nutritional Value; (ii) The Food Guide Pagoda and Building a Balanced Diet; (iii) Understanding Obesity and Its Health Risks; (iv) Making Healthy Snack and Beverage Choices; and (v) Practical Activities (e.g., comparing brown and white rice, designing a healthy lunch box). To ensure consistency and quality, teachers will receive a two-hour training workshop and a detailed lesson plan kit prior to the intervention. Research assistants will conduct random spot checks (via classroom observation or lesson recording review) to monitor fidelity to the protocol.

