##### Parent engagement

2.4.3.2

Parents or guardians will receive nutrition education through two WeChat messages per month (totaling six sessions) sent via class group chats. The messages will cover practical topics such as home cooking methods for coarse cereals, interpreting nutrition labels, and preparing healthy after-school snacks. Additionally, four live webinars focusing on child nutrition and weight management will be hosted by project nutritionists and scheduled on weekday evenings to maximize accessibility. To encourage home environment support, school principals and teachers will also receive summarized briefings on the key messages. Parent engagement will be monitored through metrics such as message read-receipt rates and webinar attendance logs.

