#### Control group

2.4.4

Students in the control schools will continue to receive standard school meals without coarse-cereal substitution and will not receive any nutrition education during the intervention and follow-up periods. To ensure ethical rigor, the control group will be provided with access to the same educational materials (including lesson recordings, lesson plans, and digital resources) upon completion of the 6-month follow-up.

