#### Outcome indicators

2.5.2

Primary outcomes will be selected to assess the direct effect of increased coarse-cereal intake on overweight and obesity. Secondary outcomes, including indicators related to metabolism and gut microbiota, will be measured at baseline (T0) and at the end of the intervention (T1, 3 months).

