### Future directions and practical applications

3.3

To evaluate long-term effects, future studies should extend intervention and follow-up periods to 12 months, enabling assessment of sustained coarse-cereal consumption and obesity prevention. Assessing the feasibility of independent school-based provision after the intervention is critical. Adaptation for rural schools, where on-site cafeterias are often absent, may involve pre-packaged coarse-cereal snacks or parent-led meal preparation while maintaining the 50 g daily target. These strategies could reduce rural–urban disparities in childhood obesity and align with China’s Rural Compulsory Education Student Nutrition Improvement Program.

Subgroup analyses by gender and baseline weight status could refine intervention targeting, focusing on high-risk populations if differential efficacy is observed. Linking gut microbiota changes to metabolic outcomes, such as insulin sensitivity and lipid profiles, may support development of microbiome-informed, personalized interventions.

If proven effective, the findings and resources from this study are intended to inform practical applications and policy. The standardized resources developed, including the recipe library, digital monitoring tools, and staff training protocols, could be consolidated into a “Coarse-Cereal School Toolkit” for broader adoption. The toolkit would provide a tangible pathway for integrating coarse cereals into national policies, such as an update to the Nutritional Guidelines for Student Meals (24), potentially mandating or strongly recommending the inclusion of coarse cereals in school meal programs.

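### Two sentences state the target as the effect of coarse-cereal intake or the 50 g substitution, but the contrast is substitution plus education versus neither, so a cereal-specific effect is not identified

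*Protocol article*

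**What the plan says.** Two places in the protocol article name cereals alone as what is assessed.

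- Section 2.5.2 (Outcome indicators, in the Methods): "Primary outcomes will be selected to assess the direct effect of increased coarse-cereal intake on overweight and obesity".
- Section 3.1 (Rationale and significance): the trial is "designed to evaluate the real-world effectiveness of a daily 50 g coarse-cereal substitution" for obesity prevention in primary school children.

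The arms differ in more than cereals.

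- Section 2.4.1 gives the intervention school a "daily coarse-cereal intervention incorporated into school meals, combined with structured nutrition education for students and parents".
- Section 2.4.3.1 adds seven student sessions of about 45 minutes. Besides coarse cereals and a balanced diet, the topics include obesity and its risks, and "Making Healthy Snack and Beverage Choices".
- Section 2.4.3.2 adds six WeChat sessions for parents, covering nutrition labels and after-school snacks among other topics, and "four live webinars focusing on child nutrition and weight management".
- Section 2.4.4 leaves the control school on standard meals without substitution; its students "will not receive any nutrition education during the intervention and follow-up periods".

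Section 3.3 then considers, if the intervention proves effective, an update of student meal guidance "potentially mandating or strongly recommending the inclusion of coarse cereals in school meal programs".

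**The concern.** Teaching children and parents about obesity, snacks, drinks and weight management can change BMI-SDS without any change in cereal intake. If the intervention school does better, the two sentences above would let the result be reported as evidence for the cereal substitution, and section 3.3 would carry it towards a provision about cereals in school meals. The education could account for part or all of the same result. A school system that adopted the cereals without the education would be adopting something the trial had not tested.

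**Working it through.** The point is about identification, so no sample-size or power figure has to be reproduced. The check sets what each arm receives against what is claimed.

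**1. Components by arm**

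| Component | Intervention school | Control school | Section |
|---|---|---|---|
| About 50 g/day coarse-cereal substitution | yes | no | 2.4.2.1, 2.4.4 |
| Student sessions (7) | yes | no | 2.4.3.1, 2.4.4 |
| Parent messages (6) and webinars (4) | yes | none described | 2.4.3.2, 2.4.3.3 |
| Number of schools | 1 | 1 | 2.2 |

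Section 2.1 specifies two arms. There is no cereal-only or education-only arm.

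**2. What the contrast estimates**

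Write c for the effect of the substitution, e for the effect of the education, i for their interaction, and s for the difference between the two schools that would exist without any intervention. The difference between arms is

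D = c + e + i + s.

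This is one equation in four unknowns. Take s = 0 and i = 0, and let D equal the planning difference of 0.17 BMI-SDS in section 2.3.1, written as a benefit. Each of these fits equally well:

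- c = 0.17, e = 0 (0.17 + 0 = 0.17)
- c = 0, e = 0.17 (0 + 0.17 = 0.17)
- c = 2 × 0.17 = 0.34, e = −0.17 (0.34 − 0.17 = 0.17)

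The third is an algebraic illustration, not a forecast. It shows that the cereal share is not confined to the range 0% to 100% once components may oppose each other or interact.

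**3. Whether a planned analysis separates c from e**

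- The mixed model in section 2.6.2 adjusts for the baseline outcome, age, sex and baseline physical activity. Assignment to education coincides with arm, so no covariate adjustment can separate it.
- The comparison of high adherence (at least 40 g/day) with low adherence (below 25 g/day) in section 2.7 is not randomised. Children who eat more of the cereals may also be those who respond more to the education.
- The dietary recall and food frequency data (2.5.1) can show which intakes changed. They do not attribute a change in BMI-SDS to one component.
- The school random effect in 2.6.2 does not remove s, because school and arm coincide.

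**4. Whether the document is consistent about its aim**

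The Abstract states the aim as a comprehensive intervention and lists the education. Section 2.4.1 defines the intervention as both components. Section 2.3.1 takes its planning difference from earlier comprehensive interventions. Section 3.1, two sentences after the one quoted, describes a combination of dietary modification, education and monitoring tools. The sentences in 2.5.2 and 3.1 are therefore out of line with the rest of the article.

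**5. Whether the Limitations cover it**

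Section 3.4 discusses duration, setting, the risk of baseline imbalance with few clusters, blinding and unmeasured confounders. It says neither that the components are inseparable nor that arm and school are the same thing.

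**The case against.** The strongest reply is that this is a disclosed package trial with loose wording in two places. Testing a package is legitimate, especially in a pragmatic trial, and the package is stated in the Abstract, in 2.4.1 and in the same paragraph of 3.1. The sentence in 2.5.2 can be read as explaining why weight-related measures are primary and metabolic and microbiota measures secondary. No mediation or component analysis is planned, so no analysis depends on the phrase about a direct effect.

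Most of that stands, and it rules out several stronger readings that a reader might infer:

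- That the design is wrong or the education concealed. The documents support neither.
- That section 3.3 draws a cereal mandate from the trial. The text is conditional on effectiveness, tentative, and tied to a toolkit of recipes, monitoring tools and staff training.
- That the Conclusion makes the same error. It speaks of a coarse-cereal intervention with multi-level engagement and makes no substitution-only claim.

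The reply does not remove the point. Section 2.5.2 is in the Methods and gives the purpose of the primary outcomes, and section 3.1 names the substitution as what is evaluated. Both attribute to the trial a property that its contrast lacks, and the Limitations do not correct this.

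**Conclusion.** The point holds as an inconsistency in the stated aim. Sections 2.5.2 and 3.1 claim a cereal-specific effect that a two-arm comparison of substitution plus education with neither cannot identify. This rests only on the arm descriptions in the article and on the absence of a third arm. It needs no assumption about how effective the education is, only that it could affect weight.

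The size cannot be given as a number. A reader might want to say that the cereal share lies between 0% and 100%, but the documents supply no such bound.

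A reader might also infer that the trial can at least conclude on the package. That goes too far. With one school per arm, even the programme effect cannot be separated from pre-existing or concurrent differences between the two schools. The combined programme is the right target to state, but the limitation has to be stated with it.

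Arms, outcomes, sample size and analysis model are unaffected by this point.

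**What to change.** 1. In 2.5.2 and in the quoted sentence of 3.1, state the target as the effect of the combined meal-substitution and education programme versus usual practice. Remove the reference in 2.5.2 to a direct effect of increased coarse-cereal intake.
2. In 3.3, tie the conditional policy statement to the combined programme.
3. In 3.4, add that component effects cannot be separated and that, with one school per arm, the programme effect cannot be separated from differences between the two schools.
4. Optionally, tabulate snack, sugar-sweetened-beverage and coarse-cereal intake by arm from the food frequency questionnaire, which section 2.5.1.2 already collects at all three time points. This shows which behaviours changed. It is descriptive and does not identify component effects.

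The Conclusion needs no substitution-specific correction. The cost is a few sentences and, if wanted, one table from data already planned. The downside is a narrower claim.
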